**There are many considerations in calculating the burden of shoulder pain:**

Measuring the burden of an illness is multifactorial and requires consideration of 1. direct costs - those directly associated with healthcare provided, 2. indirect costs, which include loss of productivity at work, around the home and the impact on others and 3. intangible elements such as pain and quality of life (Phillips et al 2006, Lubek 2003). To calculate the monetary value of shoulder pain, direct and indirect costs must be considered. These can be measured prospectively or retrospectively by interrogation of health records or through patient reports.

Period of recall in patient reported measures:

Variation exists within the published healthcare economic literature, regarding the recall period used for patient reported measures. The Outcome Measures in Rheumatology Clinical Trials (OMERAT) is an informal international network and research collaborative engaged in ongoing work to clarify contextual factors, evaluate existing measures and design at-work productivity measures for use in arthritis (Tang 2011 b, OMERACT 2012). OMERACT (2012) report that in present productivity measures, the requested recall period can vary from 2 weeks, to 2 years. The literature suggests many factors impact patient recall bias and that accuracy is sensitive to the subject matter being recalled, for example major life events have accurate recall over years, while in contrast acute pain levels or food intake may be better suited to recall periods of hours or days (Stulla et al 2005). Research specific to healthcare cost recall of musculoskeletal conditions has tended to use a period of weeks to months, with some recent and relevant studies reporting acceptable accuracy over a 3 month recall period:

Merkesdal et al 2005, Compared patient reported to healthcare funder data for RA patients every 3 months over an 18 month period and reported that patients report their productivity losses from sick leave and disability adequately.

Pinto et al (2011) reported on the comparison of patient reported and database records for healthcare costs including GP care, hospital care and medication for patients with hip or knee osteoarthritis. Over a 3 month recall period, visits, the majority of medications and overall costs reported by patients were consistent with databases.

Valuing productivity loss in unpaid activities:

Disease related changes in the productivity of unpaid activities is a form of indirect cost which ais difficult to quantify. For example, productivity whist undertaking housework, parenting, education or volunteer work, or burden upon formal or informal carers such as family or neighbours, can be impacted by a shoulder condition but there is no definitive way to monetise these impacts. The human capital approach is prone to underestimating the contribution of these intangible costs, willingness-to-pay methods have been used but these are complex, time consuming (Lubek 2003) and beyond the scope of the present study. No specific questionnaires exist to capture this information.

Valuing productivity loss in paid employment:

1) Absenteeism:

Traditionally absenteeism was the main measure of the productivity loss. The burden of absenteeism can be calculated from the societal perspective by the Human Capital Approach, which considers the value of lost production, or the Friction Cost Method which only considers that these costs only occur for a period required to replace the absent worker (Virta et al 2012, Phillips 2006). Absenteeism can be measured from employee records, records of doctor prescribed sick leave (Virta et al 2012), or patient reporting. Patient reporting is an acceptable method as previous research has found good agreement between self-reported absences and employer records with Spearman correlation coefficients of 0.79 for women and 0.75 for men (Ferrie et al 2005) shown in one study and 0.81 and 0.71 for hours missed over one and four week recall periods in another study (Kessler 2003).

2) Presenteeism:

More recently presenteeism or at-work productivity loss has increasingly been considered important. It describes reduced productivity in people who remain at work with an illness. When total reduced productivity costs are considered to be the sum of medical, pharmaceutical, absenteeism and presenteeism, Chen (2009) estimated presenteeism to account for over half of total productivity loss in arthritis sufferers. Burton (2006) found arthritis suffers had particular problems with physical aspects of work, in comparison to other aspects such as concentration or time management.

OMERACT contributors have published recent reviews of productivity measures including Tang et al (2011 a), which identified 11 measures of productivity in arthritis conditions. The Rheumatoid Arthritis Worker Instability Scale has ample validation in osteoarthritis but it is not a true measure of productivity. It measures the gap between ability and job requirements and may have prognostic value for job placement. Dedicated productivity scales with best utility for the population of the present study were:

- Work Productivity and Activity Impairment Questionnaire (WPAI): this has evidence of use in and generalisability, to many musculoskeletal conditions, is compatible with economic costing and easy to administer.
- Work Limitations Questionnaire (WLQ): this is the most widely used measure in musculoskeletal, it has excellent construct validity and the benefit of being expressed as a percentage of productivity loss in dual clinical and economic purposes.

**We propose a combination of measures to capture a baseline value for the cost burden of shoulder pain in our study population:**

To capture data about the costs of medical and related care, we have designed a direct and indirect healthcare costs questionnaire which we plan to administer with a 12 week recall period. We are presently unable to predict how many participants will be in paid employment. The literature to date suggests that the WPAI and the WLQ are best for our study population. Expert opinion suggests using a combination of measures including the WLQ (Beaton 2012). Therefore we propose to include both the WPAI and WLQ, alongside our direct and indirect costs questionnaire.

**2. Investigation of shoulder pain and range of movement immediately following injection, as predictors of longer term response to injection:**

Re-testing of shoulder clinical signs following the delivery of local anaesthetic and corticosteroid is commonly taught and practised following subacromial and other musculoskeletal injections. Advocates’ generally consider immediate or within-consultation post-injection changes, to be suggestive of the contribution of subacromial structures to a patient’s pain, and potentially suggestive of long-term response to the injection. Anecdotally, while few clinicians make ongoing management decisions based purely on this immediate response, it is common practise and therefore thought to contribute to the clinical decision making process. To date no studies have directly investigated the prognostic value of within-consultation shoulder clinical tests as predictors of a longer-term response to subacromial injection.

**Secondary Objectives**

1. To measure the economic burden of shoulder pain, for patients referred to a public orthopaedic service.

2. To explore changes in shoulder pain and range of movement immediately following shoulder injection, as predictors of longer term response to injection.

# STUDY PROGRAMME

## Design

Stage 1: Demographic and disease burden measurements. Level of agreement between two examiners (physiotherapist and surgeon who are blinded to each others decisions) regarding patient selection for injection, and forms the entry criteria for entry to stage 2,

Stage 2: Randomised Controlled Trial in which participants will see either the physiotherapist or the surgeon for their injection

***Participants***

Volunteers aged 18 and over with a referral to orthopaedics for shoulder pain, will be screened for inclusion through a clinical assessment with both the physiotherapist and the orthopaedic surgeon, who will be blinded to each others decisions (stage 1). Participants will be blinded to the profession of their examiner. Only volunteers independently deemed appropriate for 'subacromial injection today' by both the physiotherapist and the surgeon, will be invited to enter stage 2. Participants will be blinded to the profession of the clinician who delivers the injection.

**Stage 1 inclusion criteria**

- - Volunteers aged 18 years and over with a new GP referral to orthopaedics for shoulder pain

**Stage 1 exclusion criteria**

- - Previous consultation with either the research physiotherapist or the research orthopaedic surgeon for this condition
  - No XRay of the shoulder in the past 12 months

**Stage 2 inclusion criteria**

- Agreement between examiners on “would you provide subacromial injection today?”
- Participants who are able fill in the questionnaires and follow post-injection instructions

**Stage 2 exclusion criteria**

- Previous surgery to the involved shoulder
- Currently taking anticoagulant medication
- Need for prophylactic antibiotics with the injection
- Pregnancy or breastfeeding

***Outcome measures***

The shoulder pain and disability index (SPADI) has been shown to be a reliable and valid outcome measure (Beaton 96, Williams 95, Roach 91, Heald 97, Paul 04).

Participant global assessment of change from baseline will be recorded using a 5 point scale – complete recovery, better, same, worse, much worse - as used in a previous pragmatic shoulder therapy trials (Hay 03, Crawshaw 10).

*** primary outcome measure stage 1**

**^ primary outcome measure stage 2**

| **Category** | **Measure** | **From** | **Timing** |
| --- | --- | --- | --- |
| **Clinical and Demographic Characteristics** | Age, sex, employment status, hand dominance, uni or bilateral | Participant | Baseline |
| Imaging to date and key findings | Referral | Baseline |
| Duration of symptoms | Participant | Baseline |
| Past treatments and costs – physiotherapy, injection, surgery, other | Participant | Baseline |
| Medications | Participant | Baseline |
| **Baseline outcome measures** | Impact and costs questionnaire | Participant | Baseline |
| Work Productivity and Activity Impairment Questionnaire (WPAI) | Participant | Baseline |
| Work Limitations Questionnaire (WLQ) | Participant | Baseline |
| Shoulder Pain and Disability Index (SPADI) | Participant | Baseline |
| 10 cm VAS patient perception of pain over the past 3 days | Participant | Baseline |
| EuroQual-5D-5L | Participant | Baseline |
| **Stage 1** | | | |
| **Clinical agreement** | Are there any safety contraindications to injection? | Clinicians | At time of assessment |
| Are there any safety precautions regarding injection? | Clinicians | At time of assessment |
| *** Would you provide subacromial injection today?** | Clinicians | At time of assessment |
| Are there any other reasons to exclude this participant from stage 2 | Clinicians | At time of assessment |
| **Stage 2** | | | |
| **Safety** | Incidence of adverse events | Adverse event reporting mechanism | Collated throughout |
| **Access** | Current new appointment booking dates with Orthopaedics and OPSC | Research Assistant | At time of intervention |
| **Effectiveness** | **^Shoulder Pain and Disability Index (SPADI)** | Participant | 6 weeks  12 weeks |
| 10 cm VAS patient perception of pain over past 3 days | Participant | 6 weeks  12 weeks |
| Global Rating of Change Scale | Participant | 6 weeks  12 weeks |
| EuroQual-5D-5L | Participant | 6 weeks  12 weeks |
| Physiotherapy attendances post injection | eMR / Groupwise | 6 weeks  12 weeks |
| 10 cm VAS patient satisfaction with care | Participant | 12 weeks |
| **Economic** | Staff costs for each clinician | Standard pay scales | 6 weeks  12 weeks |
| Impact and costs questionnaire | Participant | Baseline |
| Work Productivity and Activity Impairment Questionnaire (WPAI) | Participant | Baseline |
| Work Limitations Questionnaire (WLQ) | Participant | Baseline |

In addition, two exploratory outcome measures will be collected before and immediately following injection:

1. active shoulder range of movement measured with a goniometer
2. VAS of pain during that movement

Although presently not validated in this population, they reflect commonly collected indicators of response in a clinical setting. This will allow us to explore their potential as predictors of longer term response to injection.

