**Primary objectives**

To discover whether:

1. there is agreement between the physiotherapist and the surgeon regarding selection of shoulder patients appropriate for subacromial injection.
2. care (subacromial corticosteroid and local anaesthetic injection) delivered by the physiotherapist is no worse than the same type of care delivered by the orthoapaedic surgeon, with respect to safety, access, effectiveness and efficiency.

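### Three of the four Stage 2 economic measures are taken only before randomisation, so efficiency can be compared by arm on staff cost and physiotherapy attendances, but not on patient cost or productivity

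*Protocol*

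**What the plan says.** The Protocol, under Primary objectives, asks whether injection care by the physiotherapist is no worse than that by the surgeon "with respect to safety, access, effectiveness and efficiency".

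The Stage 2 Economic block of the outcome measures table has four rows:

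- The first is the only one with follow-up timing: "Staff costs for each clinician | Standard pay scales | 6 weeks 12 weeks".
- The second is the cost form designed for this trial: "Impact and costs questionnaire | Participant | Baseline".
- The third is one of two published productivity scales: "Work Productivity and Activity Impairment Questionnaire (WPAI) | Participant | Baseline".
- The fourth is the other such scale: "Work Limitations Questionnaire (WLQ) | Participant | Baseline".

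The last three also appear higher in the table, among the baseline outcome measures. The Stage 2 Effectiveness block adds two measures at 6 and 12 weeks that bear on efficiency: EQ-5D-5L, and physiotherapy attendances after the injection, taken from records. The single Access row is "Current new appointment booking dates with Orthopaedics and OPSC", noted at the time of intervention.

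Recruitment and screening has the research assistant complete the baseline forms when the participant arrives. Both clinicians' assessments, Stage 2 consent and the randomisation envelope come later. The background to the secondary objectives describes the costs questionnaire as one "which we plan to administer with a 12 week recall period", and presents it with the WPAI and WLQ as a way to obtain a baseline figure for cost burden, which is secondary objective 1.

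**The concern.** A value recorded before randomisation cannot depend on which clinician later gives the injection. Listed as Stage 2 economic outcomes, the three questionnaires suggest that the trial will compare patient cost and productivity between arms. Followed as written, it will hold no data for that comparison.

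Efficiency is one of the four domains of primary objective 2, and the Benefits section says the findings are meant to help policy makers judge whether the model is safe, effective and efficient. What gets measured after the injection decides how far such a conclusion can reach. This is a matter of data collection: no analysis plan can recover costs that were never asked about.

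**Working it through.** The main check is a reading of the outcome table against the visit sequence. A short calculation then shows what precision the added data would have.

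**1. Which measures can carry an effect of allocation**

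| Measure | Table block | Timing | After randomisation? |
| --- | --- | --- | --- |
| Staff costs | Stage 2 Economic | 6 and 12 weeks | Yes |
| Impact and costs questionnaire | Stage 2 Economic | Baseline | No |
| WPAI | Stage 2 Economic | Baseline | No |
| WLQ | Stage 2 Economic | Baseline | No |
| Physiotherapy attendances | Stage 2 Effectiveness | 6 and 12 weeks | Yes |
| EQ-5D-5L | Stage 2 Effectiveness | 6 and 12 weeks | Yes |

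So 3 of the 4 economic rows, and all 3 participant-reported ones, precede randomisation. One economic row and two rows from another block follow it.

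**2. Period covered by the costs questionnaire.** With a 12-week recall, a baseline form covers the 12 weeks before the injection and none of the 12 weeks after it. The same form completed at week 12 would cover the whole follow-up. The Protocol states this recall for the costs questionnaire only; it gives none for the WPAI or WLQ, so how much of follow-up those two would cover is unknown.

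**3. Weight of what is not measured.** The Protocol's background cites two European cohorts in which sick leave made up 50% and 84% of total shoulder pain cost. It also cites an estimate that presenteeism accounts for over half of productivity loss in arthritis. Those cohorts came from primary care and the presenteeism figure from arthritis, so they indicate the likely order of importance here and do not measure it.

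**4. Number available at 12 weeks.** The planned size can be reproduced. With SD 21.7, margin 15, no true difference, one-sided alpha 0.05 and 80% power:

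- n per group = 2 × (1.645 + 0.842)² × 21.7² / 15² = 25.9, so 26; the t-based version gives 27 (power 0.806), matching the stated 54 in total.
- Allowing for 15% drop-out: 54 / 0.85 = 63.5, so 64, or 32 per group.
- Completers per group: 32 × 0.85 = 27.2, about 27.

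This calculation concerns SPADI alone. No margin or sample size is given for any economic measure.

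**5. Precision of a cost comparison with 27 per group.** The half-width of a 95% interval for a difference in means is about 1.96 × √(2/27) = 0.53 standard deviations, before any gain from baseline adjustment. Costs are likely to be skewed. The cited cohorts had 12% of patients causing 75% of total cost, and 20% causing 91%. If that held here, 0.12 × 27 = 3.2 to 0.20 × 27 = 5.4 people per arm would drive the result, so the normal approximation is only a guide.

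**6. Access.** Participants in both arms go through the same recruitment and Stage 1 assessment, then are randomised and sent straight to a room. Booking dates describe the two services and do not depend on the room to which a participant is sent.

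**The case against.** The strongest reply is that baseline timing is deliberate. The questionnaires are introduced to measure the burden of shoulder pain in referred patients, and nothing in the Protocol says they will be compared between arms. This stands, and it reduces part of the problem to misplacement: rows serving secondary objective 1 are repeated under Stage 2 Economic. It does not supply the missing follow-up data.

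A reader might infer that efficiency cannot be tested at all, or would rest on no randomised evidence. The documents do not support that. Staff costs are timed at 6 and 12 weeks, and physiotherapy attendances are individual resource use recorded after randomisation. Attendances can differ by arm, because the injecting clinician decides ongoing management and the number of sessions is discretionary.

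A reader might also infer that the staff cost comparison is settled in advance by two pay rates. The table names the source, "Staff costs for each clinician | Standard pay scales", and lists no consultation time, so the comparison may be thin. But no costing formula is given, the content of the Treatment Form is not shown, and costing detail may sit in an analysis plan that is not at hand. It remains an inference.

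On access, the objective does not say that each domain is a randomised non-inferiority test. The only margin and the only marked Stage 2 primary outcome concern SPADI, and booking dates are a sensible description of access. What remains is a caution about how they are reported.

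Finally, a cost comparison of this size will be imprecise. That is true, and it argues for estimation over a formal no-worse test, not for leaving the data uncollected.

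**Conclusion.** The point holds in a limited form. Three of the four Stage 2 economic measures are taken only before randomisation. Efficiency can therefore be compared between arms on staff cost and physiotherapy attendances, with EQ-5D-5L alongside, but not on patient cost, other care use, absenteeism or presenteeism. By the Protocol's own citations, sick leave is the largest contributor to total cost and presenteeism a major part of lost productivity.

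This rests on two readings: that the table is followed as written, and that baseline forms are completed on arrival as described. The SPADI comparison and its sample size are not affected. The amendment is worth making because efficiency is named in a primary objective and the change is small. Even then, with about 27 completers per arm, the result would be descriptive.

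**What to change.** - Add the impact and costs questionnaire, WPAI and WLQ to the 12-week participant form, and show that timing in the Stage 2 Economic block. The Budget already covers posting and return of the 6- and 12-week forms.
- Record consultation time on the Treatment Form, if it is not already there, so that staff cost can be built from time and pay rate.
- Compare 12-week costs by arm, adjusted for baseline cost, as an estimate with a confidence interval. Do not present the result as a test of no worse.
- If the questionnaires are not repeated, move the three rows out of the Stage 2 Economic block, assign them to secondary objective 1, and state that the efficiency conclusion is limited to staff cost and physiotherapy attendances.
- Report booking dates as a service-level description of access, not as a randomised comparison.

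The cost is a longer 12-week form, with some added burden and risk of non-response, and at most a time entry on an existing clinician form. To protect the primary outcome, SPADI should come first on the form. WPAI and WLQ data may come from fewer than 27 per arm, because the Protocol says the number in paid employment cannot be predicted.

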**BACKGROUND TO THE SECONDARY OBJECTIVES**

**1. The economic burden of shoulder pain for patients referred to an orthopaedic service:**

**The burden of shoulder pain in the Australian population and in the group of patients referred to Orthopaedics, is not presently known.**

Little is known of the cost burden of shoulder pain in the Australian population. No recent Australian population specific studies have investigated it’s direct healthcare or indirect costs. Two recent European studies reported varying total costs associated with shoulder pain, both studies found that a small group of patients were responsible for the bulk of total costs and that indirect costs of sick leave were the largest contributor to total costs.

- Kuijpers et al (2006) prospectively used a self administered 6 month cost-diary on 587 patients with a first episode of shoulder pain who presented to General Practice in the Netherlands. Mean costs were low at E689. 50% of these costs were attributed to the indirect cost of sick leave from paid work. They also found that a small proportion (12%) of the cohort accounted for 75% of the total costs.
- Virta et al (2012) directly tracked health records and found higher mean costs in a recent prospective cost-of-illness study of 204 Swedish shoulder patients presenting to General Practice or Physiotherapy at 3 primary health centres over a 6 month period. The cost of sick leave accounted for a large percentage of the total costs (84%), and a small group of patients produced most of the costs (in this case 20% of patients were responsible for 91% of the total costs and 44% of the healthcare costs). Mean annual total cost was estimated at E4139 per patient.

Economic burden in the subgroup of shoulder patients referred to orthopaedics has not previously been reported. The above data for general primary care shoulder populations demonstrates great variability in reported cost. Furthermore, true costs for an orthopaedic referred subgroup (such as that of the present study), may be diluted within a general primary care cohort.

**Understanding the economic burden of shoulder pain in patients referred to orthopaedics, will help evaluation of service delivery models:**

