Waiting lists for initial outpatient appointments highlight that access to orthopaedic surgeons is problematic on the Gold Coast and more broadly in the Australian public healthcare system. Quantifying the economic burden of shoulder pain, for patients referred to orthopaedics is necessary in order to quantify the true cost of time spent on the orthopaedic waiting list. It is also a necessary baseline for evaluation of alternative care delivery models.

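### The three patient-cost and work-loss measures in the Stage 2 Economic block are taken only before randomisation, so the efficiency comparison says nothing about patients' own costs or lost work after the injection

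*Protocol*

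**What the plan says.** Primary objective 2 asks whether physiotherapist-delivered care "is no worse than the same type of care delivered by the orthoapaedic surgeon, with respect to safety, access, effectiveness and efficiency". Efficiency is thus one of four domains in a comparison between arms.

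The Stage 2 Economic block of the outcome measures table has four rows:

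- "Staff costs for each clinician | Standard pay scales", timed at 6 and 12 weeks
- "Impact and costs questionnaire | Participant | Baseline"
- "Work Productivity and Activity Impairment Questionnaire (WPAI) | Participant | Baseline"
- "Work Limitations Questionnaire (WLQ) | Participant | Baseline"

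The last three already appear higher in the same table, among the baseline outcome measures. The section on recruitment and screening has the research assistant complete the baseline forms with participants on arrival. That is before the two clinical assessments, Stage 2 consent and the drawing of the envelope.

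The background to the secondary objectives reports that in two European studies "indirect costs of sick leave were the largest contributor to total costs". Of the burden estimate it says: "It is also a necessary baseline for evaluation of alternative care delivery models". It also describes a "direct and indirect healthcare costs questionnaire which we plan to administer with a 12 week recall period".

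**The concern.** A measurement made before allocation cannot be affected by who gives the injection. Listed as Stage 2 outcomes, the three rows carry no information about the comparison they sit under, and no other section schedules them after the injection.

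What is at stake is the scope of the efficiency conclusion. If one arm led to more absence from work or more privately bought care in the 12 weeks after injection, nothing in the data would show it. An SAP cannot repair this, because it cannot analyse data that were never collected.

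**Working it through.** **The plan's own figure.** The point does not depend on the sample size, but the fix does, so it was checked first. Inputs from the sample size paragraph: margin 15, SD 21.7, α 0.05, power 80%.

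- Normal approximation, one-sided 0.05: n per arm = 2 × (1.645 + 0.842)² × 21.7² / 15² = 25.9, so 26. The exact t calculation gives 27, as stated.
- Drop-out: 54 / 0.85 = 63.5, so 64.
- Stage 1: 64 / 0.5 = 128.

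The stated 54, 64 and 128 reproduce. All are set by SPADI.

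**Timing of the measures, set side by side.**

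| Measure | Baseline | 6 weeks | 12 weeks |
| --- | --- | --- | --- |
| SPADI, pain VAS, EQ-5D-5L | yes | yes | yes |
| Physiotherapy attendances | – | yes | yes |
| Staff costs (pay scales) | – | yes | yes |
| Impact and costs questionnaire | yes | no | no |
| WPAI | yes | no | no |
| WLQ | yes | no | no |

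- Economic rows taken at baseline only: 3 of 4.
- Economic rows timed after randomisation: 1 of 4. It comes from pay scales, not from participants.
- Patient-reported cost or productivity measures after randomisation: 0 of 3.

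SPADI, pain VAS and EQ-5D-5L also appear twice in the table, but their second entry carries follow-up times. For the three economic instruments the second entry repeats Baseline. Either the timing or the placement is wrong.

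**Period covered.** With a 12-week recall, a costs questionnaire completed on arrival describes the 12 weeks before the injection. The same form at the 12-week follow-up would describe the 12 weeks after it. The protocol states a recall period for this questionnaire only, not for the WPAI or WLQ.

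**What follow-up cost data could support.** With 27 per arm, the half-width of a 95% interval for a mean difference is about 1.96 × √(2/27) = 0.53 SD, by a normal approximation. The protocol says it cannot predict how many participants will be in paid work. If about half are (an assumption), 14 per arm gives 1.96 × √(2/14) = 0.74 SD for work measures. Costs are also highly skewed. In the Dutch cohort 12% of patients carried 75% of costs, and in the Swedish cohort 20% carried 91%. In an arm of 27 that is 0.12 × 27 = 3.2 to 0.20 × 27 = 5.4 people. The arm mean would rest on a handful of participants, and the protocol gives neither a cost SD nor a cost margin. Such data can describe a difference but are unlikely to establish that care is no worse.

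**The case against.** Baseline collection was deliberate. The background introduces the three instruments to obtain a starting value for cost burden, which is secondary objective 1 and involves no comparison of arms. For that aim the schedule is complete. This stands, but it does not explain why the rows are repeated as Stage 2 Economic measures.

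The protocol never defines efficiency or commits to a societal perspective. Much of its service-model background concerns hospital cost, waiting times and patient flow. Staff costs, physiotherapy attendances and EQ-5D-5L are all recorded after the injection. This also stands. A reader might infer that no economic comparison is possible; the documents do not support that, since a provider-side comparison survives.

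The remark about a necessary baseline for evaluating delivery models can be read as referring to service evaluation generally. It is not a promise of a before-and-after comparison within the trial, and the point does not rely on it.

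A reader might also take the cited sick-leave shares, 50% in the Dutch cohort and 84% in the Swedish one, as the fraction of the relevant cost left unmeasured. They are shares of total illness cost in primary care. They are not shares of a difference between two injectors whose patients receive the same drug schedule, advice and offer of physiotherapy. The protocol itself warns that primary-care figures may not represent patients referred to orthopaedics. Nor do the shares cover out-of-pocket costs.

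Finally, a reader might infer that the trial would report no economic difference. Staff costs come from the pay scales of two professions and may well differ. On patients' own costs and work loss the trial would be silent, which is not a report of equality.

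**Conclusion.** The point holds in a limited form. Three of the four Stage 2 Economic rows precede randomisation and cannot contribute to the efficiency part of primary objective 2. They do serve the burden objective. As scheduled, any efficiency conclusion can cover provider-side costs, with EQ-5D-5L on the effect side, but not patients' own costs or work loss after the injection.

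The size is a count, 0 of 3 patient-reported cost or productivity measures after randomisation. The documents allow no estimate of the between-arm cost difference that would be missed. The cited cohorts show only that work loss is a large part of total burden, and so is worth either measuring or expressly excluding.

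The conclusion assumes that the table's timing column is the collection schedule, and that baseline means the arrival visit described under recruitment and screening.

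**What to change.** Preferred: change the timing of the Impact and costs questionnaire to baseline and 12 weeks, and do the same for the WPAI and, for participants in paid work, the WLQ. Put the forms in the 12-week mail-out. The budget already provides for posting forms at 6 and 12 weeks, with reply-paid return for about 64. State the recall period of the WPAI and WLQ. If it is shorter than 12 weeks, a single administration covers only the end of follow-up. Report arm differences adjusted for baseline, with confidence intervals that allow for skew, and label them descriptive.

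Cost: extra pages in one existing mailing to 64 people, and data entry. There are two downsides. The added burden could slightly lower SPADI return, for which 15% drop-out is allowed. Completion would also change from assisted at baseline to postal at follow-up, which weakens within-person change but affects both arms alike.

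Otherwise: delete the three rows from the Stage 2 Economic block, keep them as baseline burden measures, and state in primary objective 2 that efficiency means provider-side costs. This costs nothing in data collection. It gives up any statement about patient or work costs by arm.
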